**Methods/design:**

This study is a double-blind, randomized, placebo-controlled trial, which will be conducted among recreational runners of Tabriz stadiums, Iran. Thirty-four recreational runners will be selected, and participants will be assigned randomly to two groups: to receive 500 mg TT supplement or placebo capsules twice daily for 2 weeks. Both groups will do high-intensity interval training (HIIT) workouts during the study. Baseline and post-intervention body composition, muscle pain, and aerobic and anaerobic performance will be assessed. In addition, assessment of malondialdehyde (MDA), total antioxidant capacity (TAC), total oxidant status (TOS), superoxide dismutase (SOD), glutathione peroxidase (GPx), uric acid (UA), 8-iso-prostaglandin F2α (8-iso-PGF2α), protein carbonyl (PC), catalase (CAT), glutathione (GSH), nitric oxide (NO), high-sensitivity C-reactive protein (hs-CRP), interleukin-6 (IL-6), interleukin-10 (IL-10), tumor necrosis factor-alpha (TNF-α), creatine kinase (CK), myoglobin (MYO), lactate dehydrogenase (LDH), insulin-like growth factor-1 (IGF-1) irisin, cortisol, and brain-derived neurotrophic factor (BDNF) will be done during three blood samplings. Changes in oxidative stress, anti/inflammatory biomarkers, and sports performance will be assessed as primary outcomes.

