**Fig. 1 Fig1:**
[figure not shown]
Study protocol diagram. TT, *Tribulus terrestris*; HIIT, high-intensity interval training; VAS, visual analog scale. -t1: 1 week pre-allocation, t0: allocation, t1: at the beginning of the study, t2: 2 weeks after the study beginning, and tx: 24 h after t2

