### Exercise protocol

This trial will use a HIIT exercise protocol as a high-intensity exercise activity designed for recreational runners using the American College of Sports Medicine (ACSM)’s physical activity recommendations [28]. The participants will do the HIIT program for two weeks (5 training sessions per week; a total of 10 sessions during the study period). A 15-min warm-up (with a variety of stretching, flexibility, walking, and running) will be included in each session. The main activity of both groups consists of two sessions with 3–4 repetitions and 30 s of running with an intensity of 90–100% of the heart rate reserve (HRR) (pressure perception 16–19) in each repetition. After each repetition and after each period, there will be 90–180 s and 2.5–4 min of active rest, respectively (active rest in the range of 40-50% of HRR) [29]. A 5-min cool-down at 45% HRR will end the training session.

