### Adherence and compliance to the protocol of the study

There will be a one-week run-in period before study initiation. The study team will monitor participants daily during the trial, and any occurrence of adverse events will be reported. Participants will be asked to return any unused capsules to assess their level of compliance and adherence. Subjects will receive supplements every week and will be asked to bring all remaining ones of their last visit. If less than 90% of the capsules were used, the person would be excluded from the analysis. Besides, the adherence to the training program will be assessed by the number of sessions attended. If less than 90% of training sessions were attended each week, the person would be excluded.

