### Laboratory investigations

#### Blood sampling

Blood sampling will be done during three stages; before the intervention, immediately after the last training session on the fourteenth day, and 24 h after the previous training session. A 10-mL blood sample will be obtained during the three stages: before the intervention, immediately after the last training session on the fourteenth day, and 24 h after the last training session by a lab technician. Plasma centrifugation will be carried out at a speed of 1500 RPM for 20 min. Then, the plasma will be collected into separate micro-tubes and placed in a freezer at a temperature of − 70 °C before laboratory analysis.

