#### Statistical analysis

Statistical analysis will be done using SPSS version-24 software (SPSS, Inc. Chicago, IL, USA). Regarding the missing values, the data analysis will be subjected to intention-to-treat (ITT) analysis. We will use the multiple imputation approach to perform ITT. The Kolmogorov-Smirnov test and Q–Q plot will be used to examine the normal distribution of variables. In order to compare the baseline value of quantitative and qualitative variables, the *t*-test and chi-square test will be used. To determine the change of variables at baseline and after the intervention, the paired sample *t*-test will be conducted. The mean change of the placebo and intervention group variables will also be compared using an analysis of covariances after adjusting the confounding variables. Mann-Whitney test will be used for quantitative non-normal variables. In order to compare the mean changes of the baseline and end of the trial, the paired-sample *t*-test and Wilcoxon test will be used for normal and non-normal data, respectively. Regarding repeated measured variables (three-time measurements), a two-way analysis of variance (ANOVA) with the Sidak post-hoc test will be applied to assess the time × group interactions. Also, the Mauchly sphericity test will be used to determine data homogeneity; in presence of a violation, the Greenhouse-Geisser adjustment will be used. *P* < 0.05 will be considered statistically significant in all tests. Furthermore, it is notable that in the case of non-normally distributed data, we will do Log transformations.

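### The weekly attendance rule excludes a runner for one missed session without saying from what, and on either reading it undermines the promised ITT analysis

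*Protocol article*

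**What the plan says.** All references are to the protocol article.

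- **Adherence and compliance, capsules:** "If less than 90% of the capsules were used, the person would be excluded from the analysis".
- **Adherence and compliance, training:** the next rule in that section reads "If less than 90% of training sessions were attended each week, the person would be excluded". It names neither what the runner is excluded from nor when the exclusion takes effect.
- **Exercise protocol:** "5 training sessions per week; a total of 10 sessions during the study period".
- **Fig. 1 legend:** the times from the start onwards are "t1: at the beginning of the study, t2: 2 weeks after the study beginning, and tx: 24 h after t2". None falls at the end of week 1.
- **Blood sampling:** samples are taken "before the intervention, immediately after the last training session on the fourteenth day, and 24 h after the last training session by a lab technician".
- **Abstract, Methods/design:** "Baseline and post-intervention body composition, muscle pain, and aerobic and anaerobic performance will be assessed".
- **Statistical analysis:** "Regarding the missing values, the data analysis will be subjected to intention-to-treat (ITT) analysis", followed by "We will use the multiple imputation approach to perform ITT".

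The article does not say whether a runner who falls below 90% is still measured at two weeks and 24 h later. It also does not say how the two adherence rules fit with ITT.

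**The concern.** Both adherence rules act after randomisation. An ITT analysis keeps every randomised runner in the assigned arm whatever their adherence, so rules that remove runners for poor adherence pull against it. The training rule adds a second problem. Because it is judged weekly, it could be applied at the end of week 1, before any follow-up outcome has been measured.

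Bias is the main thing at stake. Muscle pain, CK, LDH, myoglobin and performance are all listed under the primary objective, and soreness or injury is a plausible reason to miss a session. Exclusion may therefore be related to the primary outcomes. If the supplement affects soreness, exclusion may also differ between arms. The comparison would then no longer be the randomised one, although it would carry the ITT label.

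**Working it through.** **1. The plan's own figure.** Inputs from Sample size: difference 1128.4 U/L, SD 871.05 U/L, 95% confidence (taken as two-sided alpha 0.05), power 90%, drop-out 15%. The exact t calculation needs 14 per group (power 0.910), and 14 / (1 − 0.15) = 16.5, rounded up to 17. The stated 17 per group reproduces and is not in dispute.

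**2. What triggers the training rule.** Missing one of five sessions gives 4/5 = 80%, which is below 90%. In practice the weekly rule demands full attendance. Judged over all ten sessions, one miss would give 9/10 = 90% and pass.

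**3. Two readings of the rule.**

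| Reading of *excluded* | Data on a runner excluded in week 1 | Consequence for ITT |
|---|---|---|
| Withdrawn from the trial | Baseline only, since all follow-up is at t2 (two weeks) and tx (24 h later) | Every follow-up value is imputed |
| Dropped from the analysis, as in the capsule rule | Follow-up data can exist but are not used | Direct contradiction |

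On the first reading, imputation can use only baseline, arm and the runners who were measured. That adds essentially no information on the difference between arms, so the estimate is close to a completers' analysis. It is valid only if the missed follow-up is missing at random given those variables.

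**4. How many runners.** The documents give no attendance rate, so the miss rate m per session is an assumption, taken as equal for all runners and independent between sessions. Week-1 exclusion is 1 − (1 − m)^5. Exclusion in either week is 1 − (1 − m)^10.

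| m (assumed) | Week 1 | Per arm of 17 | Of 34 | Either week |
|---|---|---|---|---|
| 1% | 4.9% | 0.8 | 1.7 | 9.6% |
| 2% | 9.6% | 1.6 | 3.3 | 18.3% |
| 5% | 22.6% | 3.8 | 7.7 | 40.1% |

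**5. Against the drop-out allowance.** Setting 1 − (1 − m)^10 = 0.15 gives m = 1 − 0.85^(1/10) = 1.6%. Above that rate, exclusions for attendance alone use up the whole 15%. For week 1 alone the corresponding rate is 1 − 0.85^(1/5) = 3.2%.

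**The case against.** A reader might infer that a runner who misses a session in week 1 leaves the trial at that point. The article does not say so. *Excluded* has no object, and the rule follows the capsule rule in parallel form, so it can equally be read as exclusion from the analysis. The words on each week set the period over which attendance is judged, not the moment of removal. This stands, and the point is therefore made on both readings.

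A reader might also infer that such a runner has no last training session and so cannot be sampled. That too depends on the unstated removal. Someone who misses one session in week 1 could train throughout week 2 and be sampled on day 14 as planned.

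Nor is multiple imputation impossible without follow-up data from the runner concerned. It can be run, and the weak point is its missing-at-random assumption. That the runners lost would be those with most muscle damage is plausible but not documented.

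The counts may lean high. Entrants have run at least three days a week for two years, there is a run-in week, and the team monitors daily. If attendance varies between people, the chance of at least one miss is lower than under a common rate with the same mean. At 1% to 2% missed, week-1 exclusion stays inside the 15% allowance. That allowance protects power, however, and does nothing about bias.

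Finally, a condensed article may leave follow-up after non-adherence to the full protocol. Silence alone would be no finding. Here the article itself states exclusion rules that do not fit the analysis it promises.

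**Conclusion.** The point holds in this form: the adherence rules and the ITT statement cannot both be followed as written. For capsules the conflict is explicit. For training it is either the same direct contradiction or, if runners are withdrawn, a loss of follow-up data that no later analysis plan can recover.

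The size cannot be fixed from the documents. Under the assumed independent miss rates of 1%, 2% and 5% per session, week 1 alone would exclude about 5%, 10% and 23% of runners. The direction and amount of any bias are unknown. They depend on why sessions are missed and on whether this differs by arm. The documents do not establish that runners leave in week 1, so that should not be reported as what the plan states. The conclusion does not depend on it. The change should be made before the first participant starts; Trial status says the trial has not yet begun.

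**What to change.** 1. **Adherence and compliance:** state that low capsule use or attendance neither ends follow-up nor removes a runner from the ITT set, and that the two 90% rules define only a secondary per-protocol analysis.
2. **Outcome measurements and Blood sampling:** state that every randomised runner who has not withdrawn consent is measured at t2 and tx. For anyone not training that day, use the calendar definition of these times already in the Fig. 1 legend. Record time since last exercise and the reason for non-attendance.
3. **Statistical analysis:** keep multiple imputation for values that could not be obtained, and let the model use the recorded reason and timing.

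**Cost:** changes of wording, and visits already scheduled, for what is likely to be a small number of runners. There is one real downside. Exercise-responsive markers such as CK, myoglobin, LDH and IL-6 reflect a different state when no session precedes the sample. They may shift systematically as well as vary more, and if missed training differs by arm this could itself affect the comparison. A prespecified sensitivity analysis should address it.

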### Participants’ recruitment

The study population will include volunteer participants who have the eligible criteria. A total of 34 recreational runners (each group 17) will be recruited by advertisements from Tabriz stadiums, Iran. The volunteers will be screened by an initial face-to-face screening visit. In an organized meeting, participants will be provided with information, including the study procedure, requirements, possible risks, and benefits. A participant information sheet detailing study aims and requirements will be provided too.

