### Sample size

The sample size was estimated using PASS software (version 15) based on CK changes as the primary outcome of the Ma *et al.* study. Considering the mean difference of 1128.4 units of enzyme activity per liter (U/L) between the two groups and also the SDs average of 871.05 U/L, the sample size was calculated [24]. A total of 17 recreational runners were calculated to be involved in each group with a 95% confidence level, a power of 90%, and considering the additional drop-out rate of 15%.

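### With five sessions a week, the 90% weekly attendance rule means 10 of 10 sessions; if it removes runners from the analysis, it contradicts the ITT plan and can exhaust the 15% drop-out allowance

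*Protocol article*

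**What the plan says.** Four places in the protocol article bear on this.

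- **Exercise protocol** fixes the schedule: "5 training sessions per week; a total of 10 sessions during the study period".
- **Adherence and compliance to the protocol of the study** sets the attendance rule: "If less than 90% of training sessions were attended each week, the person would be excluded". The sentence on capsules in the same section is more explicit about the consequence: "If less than 90% of the capsules were used, the person would be excluded from the analysis". The attendance sentence does not say what the runner is excluded from.
- **Sample size** derives 17 per group from a creatine kinase difference ("Considering the mean difference of 1128.4 units of enzyme activity per liter (U/L) between the two groups") and "the SDs average of 871.05 U/L", "with a 95% confidence level, a power of 90%, and considering the additional drop-out rate of 15" per cent.
- **Statistical analysis** commits to intention-to-treat, with multiple imputation for missing values.

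The article gives no expected attendance rate.

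**The concern.** A threshold of 90% suggests that some absence is tolerated. Judged weekly on five sessions it tolerates none, because no attainable value lies between 80% and 100%. A randomised runner who misses one session in two weeks meets the exclusion criterion.

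Three things are at stake.

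- **Analysis population.** Dropping such runners from the analysis is incompatible with the intention-to-treat commitment, and the article does not say which governs.
- **Precision.** The drop-out allowance would have to cover this rule, the capsule rule and ordinary withdrawal together.
- **Bias.** Exclusion happens after randomisation. Muscle pain and creatine kinase are both in the primary objective. If a runner misses a session because of soreness, exclusion depends on something close to the outcome and possibly on the arm.

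**Working it through.** **1. What the rule requires.** With five sessions, weekly attendance can only be 0, 20, 40, 60, 80 or 100%. One miss gives 4/5 = 80% < 90%. Only 5/5 passes, and it must be met in both weeks, so the requirement is 10/10. Judged over the two-week total instead, 9/10 = 90% would pass.

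**2. Reproducing the sample size.** Inputs from the Sample size section: difference 1128.4 U/L, SD 871.05 U/L, 95% confidence, 90% power, 15% drop-out. A two-sided test is assumed, since sidedness is not stated.

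- Standardised difference: 1128.4 / 871.05 = 1.295.
- Two-sample t-test, two-sided 5%, 90% power: 13.56, rounded up to 14 per arm (power at 14 is 91.0%).
- Drop-out: 14 / 0.85 = 16.47, rounded up to 17 per arm.

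The stated 17 reproduces. It leaves room for 17 − 14 = 3 losses per arm from all causes.

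**3. Attendance the allowance needs.** Let p be the probability of attending any one session. If misses are independent, the proportion meeting the rule is p^10.

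- To lose no more than 15%: p ≥ 0.85^(1/10) = 0.984.
- To retain an expected 14 of 17: p ≥ (14/17)^(1/10) = 0.981.

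Both figures leave nothing for capsule exclusions or withdrawals.

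**4. Range of consequences.** Because the article gives no attendance rate, p is an assumption. Expected number retained is 17 × p^10. Power is that of the t-test at a standardised difference of 1.295, averaged over binomial retention in each arm, with excluded runners removed from the analysis.

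| Attendance per session | Lost to this rule | Retained per arm | Average power |
|---|---|---|---|
| 99% | 9.6% | 15.4 | 93% |
| 98% | 18% | 13.9 | 90% |
| 97% | 26% | 12.5 | 87% |
| 95% | 40% | 10.2 | 77% |

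**5. Sensitivity to independence.** If misses cluster in a few runners, fewer are lost at the same mean attendance. A beta-binomial model with an assumed within-runner correlation of 0.3 retains 92% at 98% attendance, 88% at 97% and 80% at 95%, against 82%, 74% and 60% under independence. On that assumption, the rule alone stays within 15% at 97% but not at 95%.

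**6. The same 90% on the two-week total.** Retention is p^10 + 10 × p^9 × (1 − p). At p = 0.95 this is 0.599 + 0.315 = 0.914, or 15.5 per arm. At that attendance, judging the rule weekly raises the expected loss from about 9% to about 40%.

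**The case against.** The strongest reply is that the harm depends on an attendance rate nobody has stated. The study is short, and the runners have trained at least three days a week for two years and have agreed to cooperate. There is a one-week run-in, and the team monitors participants daily. Attendance of 98 to 99% is not absurd, and there the planned power is kept. Clustered misses soften the loss further. A reader might infer that the 15% allowance cannot absorb the rule, or that realistic attendance would remove far more than 15%. The documents support neither: the allowance holds above about 98.4% under independence, and average power is still about 90% at 98%.

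A second reply is that intention-to-treat with multiple imputation keeps these runners in, so no power is lost. That would be right if outcomes were still collected and the attendance rule had no effect on the main analysis. But the capsule sentence in the same section removes people from the analysis in so many words, so this reading cannot be taken for granted. If follow-up stops at exclusion, imputation does not restore the lost information.

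A third reply is that selection towards less sore runners is undocumented. That stands: no section links soreness to attendance. The bias is a possibility, not a finding.

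Finally, full attendance may be what the investigators want in a two-week training study. If so, the article should state 100% rather than 90%.

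None of these replies touches the arithmetic of the rule or the conflict between the two sections.

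**Conclusion.** The concern holds in a conditional form. Two parts need no assumption about attendance: the weekly 90% rule is in effect a 10-of-10 rule, and excluding runners from the analysis on that basis contradicts the stated intention-to-treat analysis.

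The effect on power is conditional. It requires that exclusion means removal from the analysis, and its size depends on attendance and on how misses are distributed. With independent misses and no other losses, average power runs from 93% at 99% attendance to 77% at 95%; clustering makes the loss smaller, and capsule exclusions or withdrawals make it larger. Bias from removing runners after randomisation is plausible if misses relate to soreness, but the documents do not establish it.

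The sample-size calculation itself is not in error. A reader might take the stated 90% power as already lost; the documents do not support that.

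**What to change.** Reconcile the Adherence and compliance section with the Statistical analysis section:

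- Keep all randomised runners in the main intention-to-treat analysis whatever their attendance, and continue to collect their outcomes.
- Use attendance only to define a per-protocol sensitivity set, judged on the two-week total as at least 9 of 10 sessions. This preserves the stated 90% and is a value ten sessions can express.
- Report attendance by arm.

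If 10 of 10 is intended, say so plainly, state what the runner is excluded from, and restate the drop-out allowance and power under that rule. Under independent misses at 95% attendance, for example, 14 / 0.599 = 23.4, so 24 per arm would be needed to expect 14 evaluable.

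The cost is a short edit to two sections. The downside is that runners with incomplete training stay in the main analysis, which may slightly dilute the estimated effect; the per-protocol set shows by how much the result changes.

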### Questionnaires

Five types of questionnaires will be completed by each subject in this study: socio-demographic, 3-day food diary (2 weekdays and one weekend day) [31], the visual analog scale (VAS) [32], International Physical Activity Questionnaire (IPAQ) [33], and the PAR-Q [27]. Initially, PAR-Q will be used as a pre-study screening questionnaire that assesses a person’s eating habits, lifestyle, medical history, and physical fitness in several items; answering yes to any items of this questionnaire means that the participant will not enter into study [27]. The demographic data (age, gender, education, marital status, occupation, and income level) will also be collected. Runners will be asked to stick to their regular diet throughout the study. Assessments of dietary records at the beginning and end of the study will be done to ensure that the individuals followed their normal routine. Dietary intake of macronutrients and antioxidants (vitamin A, vitamin C, vitamin E, lycopene, β-carotene, β-cryptoxanthin, zinc, and selenium will be assessed using Nutritionist IV software (The Hearst Corp., San Bruno, CA, USA) [31]. The physical activity level of runners will also be assessed using the IPAQ questionnaire. Based on the IPAQ scoring system, the physical activity level of participants will be classified into three types: low activity, moderate activity, and high activity [33]. Also, a VAS will be used to determine the recreational runner’s muscle pain [32]. The VAS, a tool for reporting subjective muscle pain, has been used in several studies [34, 35]. It has also been validated as a measure for chronic and experimental pains [36]. Participants will rate the level of their pain on a 1–10 scale, from “no pain” to “extreme pain” [32].

